**Fig. 1 Fig1:**
[figure not shown]
Flowchart for the cervical drainage tube trial

### Statistical analysis

All prospective data will be statistically analyzed using JMP® 11 (SAS Institute Inc., Cary, NC, USA). To evaluate the significance of differences between the two groups, Chi-squared and Fisher’s exact tests will be used as appropriate for categorical variables, and the nonparametric Mann–Whitney *U* test will be used for continuous variables. The significance level will be set at 5%.

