## Methods/design

### Study aim

This is a randomized controlled, parallel-group, noninferiority trial of nonplacement versus placement of a cervical drainage tube in patients who undergo McKeown esophagectomy for indication.

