### Objectives

Patients with resectable esophageal cancer are randomized in the outpatient clinic to either the nonplacement or placement group. The objective is to evaluate the safety and efficacy of nonplacement of a cervical drainage tube as an alternative to predictive placement of a cervical drainage tube as treatment for anastomosis leakage in McKeown esophagectomy. We hypothesize that nonplacement of a cervical drainage tube leads to a noninferior postoperative anastomotic leakage rate, duration to oral intake, hospital stay, and less analgesic use compared with placement of a cervical drainage tube, which is the current standard of care.

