### Outcome measurements

#### Primary outcome

The primary outcome of this study is the percentage of anastomotic leakage events (grade 2 or higher) based on the Clavien–Dindo classification of surgical complications [15].

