### Sample size calculation

Based on data from our own case series, the rate of Clavien–Dindo grade 2 or higher anastomosis leakage is 5%. Noninferiority is defined as a significant difference in the primary outcome between the two arms of less than 12%. Based on a one-sided type 1 error rate of 2.5% and power of 80%, the sample size needed to exclude a noninferiority margin of 12% for the difference in the proportion of participants reaching the primary outcome is 104 patients. An estimated compensation of 5% for withdrawals was added, resulting in a total of 110 patients, with 55 in each arm. Figure 1 summarizes the final study design.

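### The trial is sized to exclude a 12-point margin at one-sided 2.5%, but the only analysis stated for the binary primary outcome is a test of no difference at 5%

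*Protocol article*

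**What the plan says.** - **Design.** Study aim: "This is a randomized controlled, parallel-group, noninferiority trial of nonplacement versus placement of a cervical drainage tube". The primary outcome is the proportion of patients with Clavien–Dindo grade 2 or higher anastomotic leakage, a binary variable.
- **Sample size calculation.** From the centre's own series, "the rate of Clavien–Dindo grade 2 or higher anastomosis leakage is 5" (percent). The criterion reads "Noninferiority is defined as a significant difference in the primary outcome between the two arms of less than 12" (percent). The calculation is "Based on a one-sided type 1 error rate of 2.5% and power of 80" (percent), aimed at excluding the 12% margin, and gives 104 patients, or 110 (55 per arm) after 5% for withdrawals.
- **Statistical analysis.** This is the only section that names methods, and it opens by covering all prospective data. For categorical variables: "To evaluate the significance of differences between the two groups, Chi-squared and Fisher’s exact tests will be used as appropriate for categorical variables". Continuous variables get the Mann–Whitney test. Then: "The significance level will be set at 5" (percent), with no sidedness given. There is no confidence interval, no test against the margin and no separate method for the primary outcome. Final analysis adds no method.
- **Objectives.** The hypothesis is that nonplacement "leads to a noninferior postoperative anastomotic leakage rate, duration to oral intake, hospital stay, and less analgesic use". No margin is given for oral intake or hospital stay.

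**The concern.** The null hypothesis of the design is that nonplacement raises leakage by 12 points or more. The null hypothesis of a chi-squared or Fisher test is that the two rates are equal. Neither outcome of the second test answers the first question. A significant result can occur in either direction and at any size of difference. A non-significant result may only mean that there were few events, and at 5% leakage about 2.6 to 2.75 events per arm are expected (52 × 0.05 to 55 × 0.05).

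The criterion under Sample size calculation does not close the gap. It joins a significant difference to a threshold of 12%, and names neither a direction nor a confidence limit. It could be read as a limit on the point estimate, a limit on a confidence bound, or a significance test.

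At stake is the main conclusion. The Discussion and Conclusions plan to recommend nonplacement if the hypothesis is confirmed, on the ground that leakage would be similar. The plan as written contains no procedure that could support that statement at the error rate used to size the trial.

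**Working it through.** **Inputs.** Leakage 5% (Sample size calculation), taken as 5% in both arms; equality is an assumption, and it reproduces the stated number. Margin 12 points, one-sided 2.5%, power 80%; 52 per arm before and 55 per arm after withdrawals (same section). Tests and 5% level from Statistical analysis.

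**1. Reproduce the sample size.** With unpooled variance,

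n per arm = (1.960 + 0.842)² × [0.05 × 0.95 + 0.05 × 0.95] / 0.12² = 7.849 × 0.095 / 0.0144 = 51.8, so 52 per arm and 104 in total.

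For withdrawals, 104 / 0.95 = 109.5, or 104 × 1.05 = 109.2; both round up to 110. At one-sided 5% the total would be 82, so the stated number does rest on one-sided 2.5%. The design figure is sound under the Wald approximation.

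**2. How often each rule would pass.** All pairs of binomial counts were enumerated exactly. Chi-squared is without continuity correction. At the margin the true rates are 17% (nonplacement) and 5% (placement), so every pass is a false claim of noninferiority.

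| Rule applied at 17% vs 5% | 52 per arm | 55 per arm |
|---|---|---|
| Fisher p ≥ 0.05 | 63% | 60% |
| Chi-squared p ≥ 0.05 | 49% | 46% |
| Fisher p ≥ 0.05 and observed difference < 12 points | 53% | 49% |
| Chi-squared p ≥ 0.05 and observed difference < 12 points | 47% | 43% |
| Wald 95% upper limit < 12 points | 3.8% | 3.3% |
| Newcombe 95% upper limit < 12 points | 2.1% | 2.3% |

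At 20% vs 5% with 55 per arm, non-significance still occurs in 43% (Fisher) or 31% (chi-squared) of trials.

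**3. One observed result.** Take 9/52 vs 3/52: 17.3% − 5.8% = 11.5 points worse. Fisher gives p = 0.12 and chi-squared p = 0.066, so neither named test is significant, and the point estimate is below 12. The 95% upper limit is 23.6 points (Wald) or 24.5 points (Newcombe), about twice the margin.

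**4. Power of a margin-based analysis at 5% vs 5%.**

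| Interval | 52 per arm | 55 per arm |
|---|---|---|
| Wald | 80% | 80% |
| Newcombe | 65% | 70% |

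The choice of interval can decide the result. For 4/52 vs 3/52 the upper limit is 11.6 points by Wald (passes) and 13.1 points by Newcombe (fails).

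**The case against.** The strongest defence is that Sample size calculation governs the primary question and Statistical analysis is a generic paragraph for the remaining comparisons. The former does give a margin, a one-sided level and the aim of excluding the margin, which is the logic of a confidence limit. A two-sided 5% level also corresponds to a one-sided 2.5% level, so the 5% need not contradict the design. An analysis plan that is not shown may set out the interval and the decision rule.

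Part of this stands. The intent to exclude the margin is clear, and the 5% level is ambiguous rather than wrong in itself. A reader might also infer that a non-significant p-value will be reported as noninferiority. The article says this nowhere, so the 43% to 63% in the working describe a possible misuse, not a stated rule. Nor is non-significance near certain at the margin: under chi-squared it is the minority outcome, and at 10/55 vs 3/55 (12.7 points worse) chi-squared gives p = 0.039 while Fisher gives p = 0.073.

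The defence fails on the main point. The article does not leave the method for the primary outcome open. It says that all prospective data are analysed with the named methods, and for a categorical variable those are tests of difference. That is a wrong method stated, not a detail deferred, and the wording of the noninferiority criterion does not correct it.

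**Conclusion.** The point holds as a conflict between two sections. The sample size calculation rests on excluding a 12-point margin at one-sided 2.5%; the stated analysis tests for no difference at 5% and cannot establish noninferiority. The sample size itself reproduces, so the fault lies in the analysis and in the wording of the criterion.

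The size of the risk is conditional. If non-significance were used as the criterion, the false noninferiority rate at the margin would be about 60% (Fisher) or 46% (chi-squared) with 55 per arm, or 49% and 43% if the observed difference also had to be below 12 points, against 2.5% intended. These figures assume a placement-arm rate of 5% and independent binomial counts.

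The matter should be settled before the analysis because it decides whether the primary conclusion is valid. The use of noninferior for oral intake and hospital stay is a smaller fault of the same kind: these are secondary outcomes without a margin, tested for difference.

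**What to change.** 1. State the primary analysis as the risk difference (nonplacement minus placement) in grade 2 or higher leakage with a prespecified two-sided 95% confidence interval. Declare noninferiority only if the upper limit is below 12 percentage points, which is a one-sided 2.5% test.
2. Replace the definition of noninferiority under Sample size calculation with this rule.
3. Limit chi-squared and Fisher tests to the other categorical comparisons, and give the sidedness of the 5% level.
4. Name the interval method and restate the power to match. Wald keeps the stated 80% but has an actual error of about 3.3% to 3.8% at the margin. Newcombe holds the error at about 2.1% to 2.3% but has about 65% power with 52 per arm or 70% with 55.
5. Drop noninferior for oral intake and hospital stay, or give each a justified margin.

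Cost: a few sentences and no new data items. The change is not free under every choice: with Newcombe, either the lower power is accepted and stated, or more patients are needed to restore 80%.

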### Protocol amendments

If important protocol modifications (e.g., changes to eligibility criteria, outcomes, analyses) are required, we will communicate these to relevant parties (e.g., investigators, Research Ethics Committees/Institutional Review Boards, trial participants, trial registries, journals, regulators) by email, telephone, and letter.

### Consideration of human rights (privacy protection)

For de-identification of participant data, the principal investigator or subinvestigator will remove personally identifiable information (e.g., participant’s name, initials, address, telephone number, medical record number) from the data management. A Subject Identification Code will be used for the enrollment of the participant and completion of the CRF, and so on.

### Final analysis

The final analysis will be performed after data from the participants have been obtained and locked after the end of the follow-up period. The responsible biostatistician will prepare the statistical analysis report and submit it to the principal investigator.

### Ownership and publication of study results

The study results will be presented at a medical society meeting and then sent for publication in a medical journal in English. As necessary, the results will also be presented at Japanese medical society meetings.

## Discussion

Randomized clinical trials have demonstrated that prophylactic drains do not decrease the incidence of postoperative complications in elective hepatectomy, colectomy, and cholecystectomy [16–19]. In pancreatic head resection, drain removal on postoperative day 4 was shown to be independently associated with a lower incidence of complications, including intra-abdominal infections [20]. Ascending infections along the drain may increase the incidence of pancreatic fistula in patients with long-term drain placement. On the other hand, whether to place a drain near the cervical anastomosis after McKeown esophagectomy remains controversial, even though drains usually are inserted near the cervical anastomosis at most institutions. In 1998, Choi et al. [10] reported a randomized trial to evaluate the role of closed suction drainage for esophageal anastomosis in the neck. In that randomized controlled study of 40 patients with esophageal carcinoma who underwent esophagectomy with an esophageal anastomosis in the neck, half had a neck drain inserted at the end of the operation. The median duration of drainage was 46 h (range 36–88 h). The median amount of drainage was 63 ml (range 15–210 ml). No hematoma or seroma formation occurred in either group. Anastomotic leakage did not occur in any patients. Consequently, the benefits of closed suction neck drainage could not be demonstrated. They concluded that routine use of a neck drain for esophageal anastomosis in the neck is not necessary [10]. However, there were some limitations in that study. First, the number of patients was too small to evaluate the usefulness of a drain for anastomotic leakage as we described in the section on sample size calculation. Second, their cohort might not have been representative of patients who undergo esophagectomy in general because none of the patients had anastomotic leakage; in general, the anastomotic leakage rate in published studies ranges from 1.5% to 21% [21–25]. In the current study, we hypothesize that nonplacement of a cervical drainage tube will lead to a noninferior postoperative anastomotic leakage rate. As a result, we can omit routine placement of a cervical drainage tube which should contribute to reduce cervical pain. Conversely, if a cervical drainage tube does indeed drain the digestive juices when anastomotic leakage occurs, the Clavien–Dindo grade may improve from grade 3 or higher to grade 2. If so, we can confirm the importance of placing a cervical drainage tube around the anastomosis during McKeown esophagectomy. This randomized trial can provide further evidence to support the use or omission of cervical drainage tube placement in patients who undergo McKeown esophagectomy for esophageal cancer.

## Conclusions

This is the first randomized controlled trial comparing nonplacement versus placement of a cervical drainage tube during McKeown esophagectomy with respect to the usefulness of a drain if anastomotic leakage occurs. If our hypothesis is correct, nonplacement of a cervical drainage tube will be recommended since the anastomotic leakage rate would be similar but there would be less pain compared with the current standard care using a cervical drainage tube.

## Trial status

This is protocol version 2.1, 30 March 2018. Recruitment began on 30 March 2018, and is expected to be completed on or around 31 October 2020.

## Data Availability

The datasets obtained and/or analyzed during the current study will be available from the corresponding author on reasonable request.

## Abbreviations

CRF: Case report form
ICS: Intercostal space
IDMC: Independent Data Monitoring Committee
